### Statistical Analysis

As recommended, we will conduct both per-protocol and intention-to-treat analyses^22,23^; however, the per-protocol analysis will be considered primary. We will report the stability of the noninferiority conclusion between the per-protocol and intention-to-treat results,^22,23^ and congruence in results between these analyses will increase confidence in our interpretation of the findings. Per-protocol analyses are often preferred for addressing questions of noninferiority because compared with intention-to-treat analyses they reduce the risk of falsely declaring noninferiority when a meaningful difference between the effects of 2 interventions in truth exists. In contrast, intention-to-treat analyses are preferred for questions of superiority because they reduce the risk of falsely declaring superiority when the effects of the interventions are, in truth, similar. As outlined in the TRICS-III main protocol, the per-protocol analyses will exclude (1) patients whose adherence to the assigned transfusion strategy is less than 90% and/or (2) patients who withdraw from the study at any time (including withdrawal of the patient by their treating physician). Currently, we anticipate an estimated 10% of randomized participants will be excluded from the per-protocol analysis; this subgroup of patients will be examined carefully to assess the potential for bias in the per-protocol analysis. In the intention-to-treat analyses (described below), all participants will be analyzed according to their original randomized group assignment regardless of whether transfusion occurred or which transfusion approach was followed. We will report the unadjusted absolute risk difference between the 2 groups with a 95% confidence interval using the large-sample normal approximation for a difference in proportions. We will accept noninferiority if the upper limit of the 2-sided 95% confidence interval for the difference in proportions of acute kidney injury (proportion of acute kidney injury in the restrictive-approach group minus the proportion in the liberal-approach group) is less than the noninferiority margin of 3.5%. We expect that data on postoperative serum creatinine will be missing for <2% of participants due to death and <5% due to missing data. For patients who were randomized but are missing at least 1 postoperative serum creatinine value, we will use recommended model-based multiple imputation methods using all available data to impute acute kidney injury status.^24-26^

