#### Randomization and intervention

Patients were identified in the preoperative anesthesia or cardiac surgery clinic or in the in-patient unit at each hospital, where informed consent was obtained. Enrolled patients were randomized to receive a restrictive or liberal approach to red blood cell transfusion. Randomization was generated centrally online by the Applied Health Research Centre at the Li Ka Shing Knowledge Institute of St. Michael’s Hospital (Toronto, Ontario, Canada). Randomization was stratified by center using random permuted blocks of varying sizes. For the restrictive approach, transfusion was not initiated until a patient’s hemoglobin concentration fell below 75 g/L intraoperatively and/or postoperatively in the intensive care unit or on the hospital ward. For the liberal approach, transfusion was initiated once a patient’s hemoglobin concentration fell below 95 g/L intraoperatively or postoperatively in the intensive care unit or if it fell below 85 g/L on the ward. For each group, transfusion occurred within the following time frames of the hemoglobin trigger: within 2 hours for patients in the operating room, within 18 hours for patients in the intensive care unit, and within 40 hours for patients on the hospital ward.

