### Statistical Power

The TRICS-III study is designed to test whether a restrictive approach to transfusion is noninferior to a liberal approach. The total required sample size for the TRICS-III kidney substudy is 3378 based on a noninferiority margin of 3.5% for an absolute risk increase in acute kidney injury with the restrictive versus liberal approach, a 1-sided alpha of 0.025, and 85% power, assuming a baseline rate of acute kidney injury of 15%, <2% missing data due to death, and ~85% meeting our eligibility criteria. Thus, our projected available sample size of 4074 patients for this substudy will be adequate. A noninferiority margin of 3.5% is a reasonable minimal clinically important difference; for example, in our prior analyses of acute kidney injury within a large randomized trial, coronary artery bypass surgery done without a bypass pump reduced the relative risk of acute kidney injury by 17% (95% confidence interval, 3%-28%) compared with surgery done with a bypass pump, but without evidence of better preserved kidney function, mortality, or any other relevant clinical outcome 1 year later (with a baseline rate of 15%, a relative risk increase of 17% represents an absolute risk increase of about 2.5%).^19^

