#### Adjusted analysis

In our experience with CORONARY and POISE kidney substudies,^19,26^ the unadjusted and adjusted results were virtually identical; nonetheless, we will conduct the following mixed-effects model for binary outcome data, considering center as a random effect (randomization stratum), adjusted for several prespecified factors (measured before randomization) based on their known association with acute kidney injury in the cardiac surgery setting: age (per year), sex, hemoglobin (per 10 g/L), left ventricular systolic ejection fraction categories, diabetes mellitus, treated hypertension, and eGFR (above or below 60 mL/min/1.73 m^2^).^33-35^ We will report the adjusted absolute risk difference with a 95% confidence interval (the latter estimated using bootstrap methods).^19,36^

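### The primary noninferiority interval is valid but leaves out center and the baseline covariates already planned for the supporting model, so it is probably somewhat wider than it needs to be

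*Protocol article*

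**What the plan says.** All references are to the protocol article.

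- **Primary estimate (Statistical Analysis):** "We will report the unadjusted absolute risk difference between the 2 groups with a 95% confidence interval using the large-sample normal approximation". Noninferiority is accepted if the upper limit of the two-sided 95% interval, restrictive minus liberal, "is less than the noninferiority margin of 3.5" percentage points.
- **Design (Randomization and intervention):** "Randomization was stratified by center using random permuted blocks of varying sizes".
- **Supporting model (Adjusted analysis):** a mixed-effects model for binary data, "considering center as a random effect (randomization stratum), adjusted for several prespecified factors (measured before randomization"). The covariates are age, sex, hemoglobin, ejection fraction category, diabetes, treated hypertension and kidney function. Age is entered per year and hemoglobin per 10 g/L, but kidney function is entered as "eGFR (above or below 60 mL/min/1.73" m²). The output is an adjusted absolute risk difference with a bootstrap interval.
- **Role of that model (Other prespecified analyses):** it is one of several supporting analyses, checked for agreement with the primary result.
- **Reason given (Adjusted analysis):** in two earlier kidney substudies the adjusted and unadjusted results hardly differed.
- **Timing (The TRICS-III Trial):** no comparison of outcomes between the groups had been made when the article was written.

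**The concern.** The noninferiority decision rests on one number, the upper confidence limit, so interval width matters directly. Stratifying by center balances the groups within centers. If risk differs between centers, a crude two-proportion standard error still counts between-center variation that the design has removed from the comparison, and the interval is too wide. The same reasoning applies to covariates that the article itself selects for their association with acute kidney injury.

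The reason given for expecting little from adjustment does not settle this. The article does not say whether the earlier agreement covered interval widths as well as estimates, and agreement of estimates alone would not show that no precision is lost. Cutting eGFR at 60 also discards information. Baseline creatinine is required of every patient in the substudy, so a continuous eGFR can be had at no extra cost in data.

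At stake is a modest amount of power, plus protection against chance imbalance in measured predictors. The type I error of the test is not at stake.

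**Working it through.** **Inputs from the Statistical Power section.** The margin is 3.5 points ("based on a noninferiority margin of 3.5% for an absolute risk increase in acute kidney injury"), error and power are "a 1-sided alpha of 0.025, and 85% power", and the event rate is 15% ("assuming a baseline rate of acute kidney injury of 15"). The projected sample is 4074.

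**Assumptions not in the article.** The true risk is 15% in both groups, and allocation is 1:1. R² is the share of outcome variance explained by center and covariates; the article gives no value for it.

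**1. The article's own figure.** Required number per group = (1.960 + 1.036)² × 2 × 0.15 × 0.85 / 0.035² = 1869, or 3738 in total. The article states 3378, at which the same formula gives 81.3% power. That mismatch is a separate matter. The check below uses the projected 4074 and does not depend on it.

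**2. Unadjusted analysis at 4074.**
- SE = √(4 × 0.15 × 0.85 / 4074) = 0.01119, or 1.119 points.
- Half-width = 1.96 × 1.119 = 2.19 points.
- Power = Φ(3.5/1.119 − 1.96) = Φ(1.168) = 87.9%.

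**3. Adjusted analysis.** The variance is multiplied by (1 − R²), so SE = √(4 × 0.15 × 0.85 × (1 − R²) / N).

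To tie R² to something recognizable, take individual risks as logistic-normal with mean 15%, so that R² = Var(risk) / (0.15 × 0.85).

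| Assumed spread on the logit scale | R² | Half-width (points) | Power at 4074 | Equivalent unadjusted N |
|---|---|---|---|---|
| None (unadjusted) | 0 | 2.19 | 87.9% | 4074 |
| Center SD 0.3 | 1.1% | 2.18 | 88.2% | 4121 |
| Center SD 0.4 | 2.0% | 2.17 | 88.5% | 4158 |
| Center SD 0.5 | 3.2% | 2.16 | 88.9% | 4207 |
| Center SD 0.4 and covariate SD 0.6 | 6.4% | 2.12 | 89.9% | 4353 |
| Center SD 0.4 and covariate SD 0.8 | 9.5% | 2.09 | 90.8% | 4503 |

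The last two rows correspond to c-statistics of about 0.69 and 0.73. The equivalent N is 4074 / (1 − R²), so those rows are worth about 280 and 430 extra patients.

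**4. In terms of the decision.** The largest observed difference that still passes is the margin minus the half-width. Unadjusted, this is 3.5 − 2.19 = 1.31 points. At R² of 6.4% to 9.5% it is 3.5 − 2.12 = 1.38 to 3.5 − 2.09 = 1.41 points.

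**The case against.** The case for leaving the plan alone is substantial.

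- **The planned test is sound.** An unadjusted difference is conventional and matches the two-proportion basis of the power statement. Ignoring center after center-stratified randomization makes the interval, at worst, a little conservative, and conservatism does not raise the risk of falsely declaring noninferiority. This stands.
- **The adjusted interval will be reported anyway.** This also stands. What is in dispute is which estimate decides.
- **The gain is small and assumed.** It is about 0.1 point of half-width against a 3.5-point margin, with power already above 85%. This stands as to size. The article calls the covariates associated with the outcome; it does not call them strong.
- **Implementation is not trivial.** With 73 centers there are on average 4074/73 ≈ 56 patients and about 8 events per center. Fixed center effects could fail through separation, and standardization must be combined with multiple imputation and the bootstrap. This stands, and it is why the fix keeps the random center effect and names a fallback.

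A reader might infer three stronger things that the article does not support:

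- **That the test is biased or invalid.** It is neither.
- **That adjustment would repair the per-protocol set.** The expected 10% exclusions follow randomization and depend on adherence or withdrawal. Any imbalance they cause is potential selection, and nothing shows that seven baseline covariates capture it. The article plans a separate examination of those patients.
- **That the unadjusted test misses its power target because the per-protocol set is only 4074 × 0.9 = 3667.** Power there would be 84.3%. But the listed substudy exclusions come to under about 4%, and 4074 is 84% of the 4850 who had surgery, so the per-protocol loss may already be counted. The article does not settle this, and the point does not need it.

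**Conclusion.** The point holds as a modest efficiency improvement. The primary interval is valid but omits the stratification factor and the covariates that the article itself selects, so it is likely to be wider than necessary. Taking 15% risk in both groups, 1:1 allocation and 4074 patients, power rises from 87.9% to about 88.2-88.9% with center alone (assumed R² 1-3%). With center and covariates (assumed R² 6-10%) it rises to about 90-91%. The arithmetic is firm given R², but R² itself is an assumption. If center and covariates predict little, the gain is close to nil. The argument for acting is that the cost is low and the change can still be made without knowledge of the results.

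**What to change.** Before any unblinded between-group analysis:

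1. Make the absolute risk difference from the Adjusted analysis section the primary estimate. Obtain it as a marginal (standardized) difference, so that it targets the same quantity as now.
2. Keep center as a random effect, as planned. Enter eGFR as a continuous variable; hemoglobin already is.
3. Name a center-stratified Mantel-Haenszel risk difference with its stratified variance as the fallback if the model does not converge. On its own it would deliver only the center part of the gain.
4. State how the bootstrap interval is combined with multiple imputation.
5. Keep the 3.5% margin and the upper-limit rule, and report the unadjusted difference as support.
6. Describe the adjustment as dealing with chance imbalance in measured covariates, and make no claim that it corrects selection from the per-protocol exclusions.

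The cost is a change of wording in the analysis plan and some programming, mostly for item 4. No new data are needed.

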
#### Subgroup of preexisting chronic kidney disease

Compared with patients with preserved kidney function, patients with chronic kidney disease have a higher risk of acute kidney injury, as well as higher rates of anemia, perioperative mortality, and cardiovascular events.^27-32^ We will examine whether the presence of preexisting chronic kidney disease (primarily defined by an eGFR <60 mL/min/1.73 m2, with other eGFR cut-points examined in additional analysis) modifies the effect of a restrictive versus liberal approach to transfusion with respect to the risk of acute kidney injury.^30^ The *P* value for the interaction will be assessed by including the type of transfusion approach, an indicator variable for chronic kidney disease, and an interaction term (chronic kidney disease × type of transfusion approach) as independent variables in a regression model for binary outcome data. We will also present the absolute risk difference between intervention groups within each subgroup.

#### Other prespecified analyses

As outlined below, we will perform several supporting analyses including a complete-case analysis, an inverse probability weighted analysis, an intention-to-treat analysis, and an adjusted analysis, examining whether there is concordance with the primary analysis.^24-26^ We will also examine death as a competing outcome and examine alternative definitions of acute kidney injury.

#### Complete-case analysis

We will perform a complete-case analysis (no use of postoperative serum creatinine imputation) restricted to patients with at least 1 postoperative serum creatinine measurement (which will be over 90% of patients in the primary analysis). We may also perform an analysis restricted to those centers with over 90% of patients with complete serum creatinine measurements.

#### Intention-to-treat analysis

The intention-to-treat analysis will follow the same analytic approach as the primary analysis, but all participants will be analyzed according to their original randomized group assignment regardless of whether transfusion occurred or which transfusion approach was followed. In addition, if noninferiority is shown, an intention-to-treat superiority comparison will be performed using a 2-sided alpha of 0.05.

#### Adjusted analysis

In our experience with CORONARY and POISE kidney substudies,^19,26^ the unadjusted and adjusted results were virtually identical; nonetheless, we will conduct the following mixed-effects model for binary outcome data, considering center as a random effect (randomization stratum), adjusted for several prespecified factors (measured before randomization) based on their known association with acute kidney injury in the cardiac surgery setting: age (per year), sex, hemoglobin (per 10 g/L), left ventricular systolic ejection fraction categories, diabetes mellitus, treated hypertension, and eGFR (above or below 60 mL/min/1.73 m^2^).^33-35^ We will report the adjusted absolute risk difference with a 95% confidence interval (the latter estimated using bootstrap methods).^19,36^

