### Secondary Question

2. Does the presence of preexisting chronic kidney disease modify the effect of a restrictive versus liberal approach to transfusion with respect to the risk of acute kidney injury?

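### eGFR is only ever used as a category: continuous eGFR in the adjusted model, and one supplementary continuous interaction, would use the same data better

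*Protocol article*

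**What the plan says.** Two sections of the protocol article fix how eGFR is coded.

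- **Adjusted analysis.** The covariate list starts with "age (per year), sex, hemoglobin (per 10 g/L"), so age and hemoglobin keep their full scale. It ends with "treated hypertension, and eGFR (above or below 60 mL/min/1.73 m^2"), so eGFR becomes one yes/no term.
- **Subgroup of preexisting chronic kidney disease.** CKD is "primarily defined by an eGFR <60 mL/min/1.73 m2, with other eGFR cut-points examined in additional analysis". The interaction model contains transfusion approach, "an indicator variable for chronic kidney disease, and an interaction term (chronic kidney disease × type of transfusion approach"). Risk differences are also to be shown within each subgroup. The extra cut-points are neither named nor counted.

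Three other places set the context. The Secondary Question asks: "Does the presence of preexisting chronic kidney disease modify the effect of a restrictive versus liberal approach to transfusion" with respect to acute kidney injury. Under Patient Selection, patients without a preoperative creatinine are excluded, as are those with eGFR below 15. The main result does not involve eGFR: "We will report the unadjusted absolute risk difference between the 2 groups with a 95% confidence interval" (Statistical Analysis). The adjusted model is listed among the supporting analyses (Other prespecified analyses).

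**The concern.** Because a preoperative creatinine is a condition of entry to the substudy, a numerical eGFR can be computed for everyone analysed. The plan nevertheless treats all values from 15 to just under 60 as equal, and treats 59 and 61 as different, on the strength of one preoperative creatinine. The extra cut-points for the CKD question divide the scale elsewhere but are still categories.

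The matter counts most for effect modification, which is one of the two stated questions and the one for which power is likely to be short. If the effect of transfusion approach changes gradually with kidney function, a two-group contrast is less likely to detect it than a test on the continuous scale. In the adjusted model the issue is smaller: an inconsistency with the age and hemoglobin terms, and a little lost precision.

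**Working it through.** **Figures in the plan.** The article states no eGFR mean, spread or CKD share and no power for the interaction, so there is no figure of its own to reproduce on this point. The CKD share and the shape of the gradient below are assumptions, shown as a range.

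**1. Information kept by one cut.** Let eGFR be normal and its effect (or its modification of the treatment effect) linear. If a share q of patients lies below 60, the squared correlation between eGFR and the indicator is

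kept = φ(z_q)² / [q(1 − q)],

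where z_q is the q-quantile of the standard normal and φ its density. For q = 0.35: z = −0.385, φ = 0.370, so 0.370² / 0.2275 ≈ 0.60.

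| Assumed share below 60 | Kept | Lost |
|---|---|---|
| 15% | 0.426 | 57% |
| 20% | 0.490 | 51% |
| 25% | 0.539 | 46% |
| 30% | 0.576 | 42% |
| 35% | 0.603 | 40% |
| 40% | 0.622 | 38% |
| 50% | 0.637 | 36% |

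**2. Power of the interaction test.** A test with 80% power at two-sided 5% has an expected z of 1.96 + 0.84 = 2.80. Keeping a fraction r of the information multiplies this by √r (treating the outcome variance as roughly constant across eGFR):

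power = Φ(2.80·√r − 1.96).

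- r = 0.60: Φ(2.169 − 1.96) = Φ(0.209) ≈ 0.58.
- r = 0.637 (50% below 60): Φ(0.275) ≈ 0.61.
- r = 0.426 (15% below 60): Φ(−0.132) ≈ 0.45.

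In terms of patients, the cost is a factor 1/r: about 1.6 at a 50% share and 1.9 at 25%. The 80% is a reference value, not a claim about this trial. If modification is a step at 60, the indicator is the correct variable and nothing is lost.

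**3. Precision of the adjusted risk difference.** Inputs from the article: 15% acute kidney injury and 4074 patients (Statistical Power). Assumed: a log odds ratio of 0.3 to 0.8 per SD of eGFR, and 25% to 50% of patients below 60. With R² the share of outcome variance explained by eGFR,

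half-width = 1.96·√[4 × 0.15 × 0.85 × (1 − R²) / 4074].

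For log odds ratio 0.5 and 35% below 60:

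- no eGFR term: 2.19 percentage points;
- eGFR cut at 60 (R² = 0.0202): 2.17;
- continuous eGFR (R² = 0.0315): 2.16.

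That is 0.6% narrower. Over the whole assumed range the narrowing is 0.2% to 1.9%.

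**4. Primary analysis.** It is unadjusted, so the coding of eGFR as a covariate or modifier changes nothing.

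**The case against.** The strongest reply is that the split matches the question. The plan asks about patients with and without CKD and defines CKD as eGFR below 60. An indicator with an interaction term and subgroup risk differences answers exactly that, whereas a continuous interaction asks about a gradient. This stands, and is why the <60 test should remain the main answer.

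Second, the power loss depends on the assumed shape. Under a step at 60 the cut loses nothing, and a linear interaction would then be the inefficient choice, by the same squared correlation. This also stands. It argues for having both tests. The article gives no reason to expect a step.

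Third, the section names one main definition and labels the other cut-points additional, so there is a single main interaction test. That is right. But the extra cut-points are unspecified, overlap, and have no stated rule for reading them together; one named continuous interaction does their job with less discretion.

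A reader might infer more than the document supports:

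- *That a fixed 40% or so is lost.* No eGFR distribution is given, so only a range under stated assumptions can be defended.
- *That this share of the information on the treatment effect is lost.* The loss concerns eGFR as a covariate or modifier. The adjusted interval hardly moves and the primary result not at all.
- *That the plan would declare noninferiority whatever the kidney function once the interaction is non-significant.* It sets no such rule, and it reports risk differences by subgroup.
- *That the adjusted model leaves harmful imbalance.* In a randomized comparison any such imbalance is due to chance, and the analysis is supporting.

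**Conclusion.** The point holds as a low-priority improvement. eGFR is coded only in categories in both places, inconsistently with age and hemoglobin in the adjusted model, although the continuous value is available for everyone analysed.

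The real cost lies in the effect-modification question, and only if modification is graded. The sizes in steps 1 and 2 of the working rest on normality, linearity and an undocumented CKD share. The gain in the supporting adjusted analysis is small, and the noninferiority decision cannot be affected. Using <60 to define CKD is not an error.

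**What to change.** - **Adjusted analysis:** enter eGFR as a continuous term, linear or as a restricted cubic spline, in place of the binary term.
- **Subgroup of preexisting chronic kidney disease:** keep the <60 interaction test and the subgroup risk differences as the main answer. Replace the unspecified additional cut-points with one prespecified supplementary interaction of transfusion approach with continuous eGFR, and plot the risk difference across eGFR.

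The cost is some wording, a change of one model term and one supplementary model, with no new data or patients. The section on the TRICS-III trial says that no between-group outcome analyses had yet been done, so at that point the change could still be prespecified.
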